### Sample

The participants are patients aged > 50 years assigned to PHC from different locations: Barcelona city (1,200,066), the central area of Catalonia (192,000), and the southern area (132,000). Such a territorial representation provides patients from urban, semi-urban, and rural areas.

Inclusion criteria are: 1) the presence of at least one of the following physical diseases: diabetes mellitus type 2, COPD, asthma, and ischemic cardiopathy; 2) a score > 12 on the Beck Depression Inventory score (BDI-II) [21, 22] Spanish version adapted by Sanz et al. [23–25], and confirmation of major depression according to DSM-IV criteria with the Mini International Neuropsychiatric Interview (MINI); 3) adherence to a one-year follow-up with the same PHC team; 4) signed informed consent.

Exclusion criteria are: 1) diagnosis of dementia or moderate/elevated cognitive decline (5 or more errors on the Pfeiffer scale); 2) major depressive disorder with psychotic symptoms or other serious psychiatric comorbidities; 3) elevated/moderate risk of suicide (a score of ≥6 on the MINI scale); 4) drug of abuse dependence disorders (including alcohol); 5) physical illness at an advanced stage; 6) inability to attend the PHC; 7) under psychological therapy from the Community Mental Health Team; 8) inability to understand Spanish/Catalan.

Patients receiving anti-depressive/anxiolytic treatment are not excluded. Their data are collected and considered as covariables.

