### Recruitment process

The recruitment process for the trial began in September 2017. All eligible PHC located in Barcelona city, the central area of Catalonia (Bagés, Berguedá, and Solsonés) and the southern area (Baix Llobregat Nord) have been contacted and encouraged to participate in the study. The PHC who express interest receive a team presentation, explanatory dossiers, and informed consent papers. Those who wish to take part are required to consecutively recruit 16–24 patients who, after meeting inclusion criteria and signing the informed consent, will be randomized into two equally sized groups (IG and CG).

Different groups of healthcare workers will be involved in the field work:Recruiters: the patient’s assigned doctor and/or nurse.Nurses leading the psycho-educational groups, two per PHC.Evaluators blinded to the groups who carry out interviews at baseline, and at 3 months, and 12 months post-intervention.An external researcher in charge of patient randomization which is performed once all the necessary number of patients have signed the consent forms. The data gathering phases are explained in the work plan section.

All outcome variables will be assessed three times: prior to study commencement (baseline), after 3 months, and at 12 months after inclusion in the individual data collection sessions. Information about data collection and intervention programme timeline are detailed in the Table 2.

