Sex, age, civil status, educational level (without studies / incomplete primary ones / completed primary ones / secondary ones / higher education), employment status (employed / housewife / unemployed / disabled / retired). Assigned PHC: rural (doctor’s surgery) / semi-urban (PHC with a population < 15,000 inhabitants) / urban (PHC with a population ≥ 15,000 inhabitants).

Primary outcomes*Clinical remission and/or response of depression* at short and long-term (one year follow-up) of the intervention following Riedel et al. [32]: clinical remission considered as a reduction in the rating < 13 of the BDI-II; response to the intervention as a decrease of at least 50% in the initial evaluation of depressive symptoms according to the BDI-II.

Secondary outcomes

*Improvement in the control of the chronic pathology* at 12 months follow-up:
Diabetes mellitus: controlled with glycosylated hemoglobin, HBA1C (%) [33, 34].COPD: lung function measured by post bronchodilator expiratory volume (FEV1). Dyspnea evaluated by the modified score of the Medical Research Council (mMRC), at 5 points [35, 36]Asthma: lung function measured by post bronchodilator expiratory volume (FEV1). Determination of peak expiratory flow (PEF) [37].Ischemic cardiopathy: measurement of levels of low-density lipoprotein cholesterol and blood pressure [38].
2.*Adherence to medication* is assessed by the *Morinsky-Green* test [39] and the comparison between containers collected in the pharmacy and those prescribed. It will be performed for all the prescribed medication for both groups.3.*Quality of life* as measured with the *EuroQol (EQ-5D-5 L)* questionnaire. (Original: EuroQol Group 1996. Spanish adaptation: Badia et al. 1999) [40, 41].4.*Utilization of healthcare services* during the study period. This includes: number of hospital admissions (emergency room and ward) due to complications arising from diabetes, COPD, and ischemic cardiopathy (yes/no), and psychiatric pathology (yes/no); mental health referrals (yes/no) and number; and consultations with the family doctor/nurse (yes/no) and number.5.*Variables resulting from the intervention with respect to its feasibility.* A questionnaire with 10 items and a Likert scale of 4 categories regarding satisfaction is administered to the patients on completing the intervention. Adherence is assessed through the number of sessions each IG patient attends. An adherence variable is calculated for the intervention: ≥75% attendance or less.

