### Statistical analysis

The analysis is performed on an intention-to-treat basis. All the patients who have signed the informed consent and attended the initial interview are included. Missing data from the BDI-II evaluation during follow-up will be substituted by the last registered value (Last Observation Carried Forward strategy). At the beginning of the study descriptive statistics will be performed to evaluate the homogeneity between the two groups (IG and CG) with respect to demographic, clinical, and service utilization variables. In order to measure the main objective (rate of remission and response) logistic regression is employed in which the dependent variable is dichotomous (rate of remission and response). The patient’s group is the independent variable. Raw and adjusted odds ratio (OR) are calculated according to age, sex, pharmacologic treatment, and comorbidity. Repeated measure ANOVA analysis will be performed to determine the evolution of the dependent variables during follow-up. For the secondary resulting variables, control of the physical pathologies will be measured by logistic regression in which the dependent variable is dichotomous (control yes/no). The models will be adjusted in the same way as the principal one. Variable differences in the BDI-II rating and other scores with respect to baseline will be calculated. Student’s t test will be employed for the comparison between the groups’ variables and standardized effect size (SES; Kazis et al.1989) [44].

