Some limitations include the fact that the nurses who carry out the intervention are aware of the groups the patients belong to. Nevertheless, blinding of some key stages of the study, such as randomization, evaluation of outcomes/confounder variables, and statistical analysis will be maintained. Second, for a long-term follow-up under normal conditions a dropout rate of 25% is expected. In the case of missed appointments and intervention sessions it is hoped that patient adherence will be ensured through telephone calls (at least three times per appointment, one of which is 24 h prior to the appointment) unless the patient has stated reluctance to participate. Third, the patients will present varying pathologies which will increase the heterogeneity of the sample. Nevertheless, most of the patients attended at the PHC present comorbidities and their inclusion represents a greater generalization of results. Fourth, in order to avoid the effect of contamination, patients assigned to the two nurses leading the IG from the same center will be excluded. Fifth, there could be some difficulty in recruiting a sufficient number of patients.

To the best of our knowledge, this is the first study evaluating the effectiveness of a psychoeducation group intervention with patients suffering from both depression and a chronic organic pathology (diabetes mellitus, COPD, asthma, and ischemic cardiopathy) to be carried out by community nurses in a primary care setting.

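### The supportive repeated-measures ANOVA names neither outcome nor visits, and fits poorly whether it is meant for the dichotomous outcomes or for the scores

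*Protocol article*

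**What the plan says.** In the Statistical analysis section of the protocol article, three statements follow one another:

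- For the main objective, "logistic regression is employed in which the dependent variable is dichotomous (rate of remission and response").
- Next comes the longitudinal analysis: "Repeated measure ANOVA analysis will be performed to determine the evolution of the dependent variables during follow-up".
- For the secondary outcomes, "control of the physical pathologies will be measured by logistic regression in which the dependent variable is dichotomous (control yes/no").

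Only after these does the section turn to the BDI-II and other scores. It plans changes from baseline for them, compared between arms by t test. The section also declares an intention-to-treat analysis of everyone who consented and attended the initial interview. Its one missing-data rule is last observation carried forward, stated for follow-up BDI-II.

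The outcome definitions are in Measures. Remission is "clinical remission considered as a reduction in the rating < 13 of the BDI-II". Response is "response to the intervention as a decrease of at least 50% in the initial evaluation of depressive symptoms", measured on the same scale. Entry (Sample section) requires "a score > 12 on the Beck Depression Inventory score (BDI-II"). On timing, Recruitment process states: "All outcome variables will be assessed three times: prior to study commencement (baseline), after 3 months, and at 12 months after inclusion". Table 3 schedules BDI-II, HARS and EQ-5D-5L at all three times. The Discussion says that "for a long-term follow-up under normal conditions a dropout rate of 25% is expected".

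**The concern.** The ANOVA sentence stands between two statements that each call the dependent variable dichotomous. Read literally, it applies a method for continuous outcomes to yes/no outcomes, although the same section uses logistic regression for them. If baseline is included, remission and response cannot vary there.

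Reading the sentence as meaning the scores removes that problem but brings others. Classical repeated-measures ANOVA needs a value at every visit. For BDI-II the carried-forward rule supplies it, and the analysis then treats a copied value as a measurement. For the other scores nothing supplies it, so incomplete patients would fall out of an analysis declared to be intention-to-treat.

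At stake is the description of how outcomes develop over 3 and 12 months. The primary test is not at stake.

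**Working it through.** **Inputs.** Entry BDI-II above 12 (Sample); remission below 13 and response as a fall of at least 50% (Measures); planning remission rates of 40% (intervention) and 26% (control), 189 per group, 25% dropout, 252 per group and 504 in total (Sample size); visits at baseline, 3 and 12 months (Recruitment process, Table 3).

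**The plan's own figure.** 189 / (1 − 0.25) = 252 per group, and 2 × 252 = 504. The dropout inflation reproduces exactly.

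**Binary reading, with baseline as a time point.**

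1. An eligible patient scores at least 13 on a whole-number scale (the Abstract also starts its range at 13). Taking the eligibility score as the baseline score, remission is 0 for all 504 patients.
2. Response is a fall from the patient's own baseline, so at baseline it is 0 by definition.
3. The variance of a yes/no variable is p(1 − p). At baseline it is 0 × 1 = 0 in both arms. At follow-up, using the planning rates, it is 0.40 × 0.60 = 0.240 (intervention) and 0.26 × 0.74 = 0.192 (control). Equal variance over time fails.
4. Sphericity is a different condition: it asks whether the variances of the pairwise differences between visits are equal. With baseline variance 0, a common follow-up variance v and a correlation ρ between 3 and 12 months, these are v, v and 2v(1 − ρ). They are equal at ρ = 0.5. The Greenhouse-Geisser epsilon is (tr M)² / (2 tr M²), where M is the covariance matrix of the two orthonormal time contrasts; v cancels. The protocol gives no ρ, so a range is assumed:

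| Assumed ρ | Epsilon |
|---|---|
| 0 | 0.80 |
| 0.3 | 0.95 |
| 0.5 | 1.00 |
| 0.7 | 0.91 |

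The departure from sphericity is mild, or absent.

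**Binary reading, with 3 and 12 months only.** The zero-variance visit disappears, and with two time points sphericity cannot fail. The outcome is still binary and the model still Gaussian.

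**Control yes/no.** Zero baseline variance does not extend to this outcome, because entry does not require uncontrolled disease.

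**Score reading.**

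1. BDI-II: at 25% dropout, up to 0.25 × 504 = 126 patients carry a copied value. A patient lost straight after baseline contributes a flat line.
2. EQ-5D and HARS: with listwise deletion, and dropout as the only source of missing visits, up to about 126 patients are excluded and 504 − 126 = 378 remain. Any 3-month values from the excluded patients are lost as well.

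**The case against.** The strongest reply is that the sentence names no variable. The plural, and the interest in change over time, fit repeatedly measured scores at least as well as a yes/no status, and the dichotomous outcomes already have logistic regression. An article may leave variables and visits to the full protocol or SAP. The ANOVA is also supportive, and treating baseline as a repeated outcome is not in itself an error in a randomized trial.

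Much of this stands. A reader might infer more than the documents support:

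- *That the ANOVA is certainly applied to binary outcomes, with baseline included.* Neither is stated; both follow only from a literal reading.
- *That sphericity fails by construction.* It does not; epsilon is 0.80 to 1.00 over the range shown.
- *That the plan prescribes complete cases.* It does not say so. Listwise deletion is inferred from how the classical method works.
- *That 126 patients drop out of the BDI-II analysis.* They do not, because carried-forward values keep them in.
- *That the plan has no 12-month comparison between arms.* The logistic regression and the t tests of change plausibly supply it.

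The reply does not rescue the method. The article fixes the technique and not only its details, and under either meaning of the sentence a better technique is readily available. HARS is listed among the outcome measures in Table 3 but among confounders and effect modifiers in the Measures text, so its place in the longitudinal analysis needs stating too.

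**Conclusion.** The point holds in a limited form. The outcome of the ANOVA is undefined. It is binary on the literal reading, and the method is unsuitable for that outcome. On the score reading the method either counts copied BDI-II values as data or loses up to about 126 of 504 patients on the other scores, contrary to the intention-to-treat statement.

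The zero baseline variance rests on baseline being a time point and on the eligibility score serving as baseline for remission. The figure of 126 rests on the plan's 25% dropout and on listwise deletion. No bias or error rate has been calculated, so no claim is made about how far results would shift. Only a supportive analysis is affected; the change is worth making but is not critical.

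**What to change.** Replace the ANOVA sentence with two named analyses.

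- **Scores (BDI-II, EQ-5D, HARS):** a likelihood-based linear mixed model using all observed 3- and 12-month values, without carrying values forward. Include the baseline score as covariate, arm by visit, and random effects for health center and, in the intervention arm, for therapy group. State that it assumes data missing at random given what was observed. A patient with no follow-up visit contributes no outcome to this model, so the number of such patients should be reported by arm.
- **Remission and response:** a mixed logistic or GEE model on the 3- and 12-month visits only.

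Report the arm difference with its confidence interval at each visit from each model. Say whether HARS is an outcome or a covariate.

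The cost is revised wording and slightly more analysis work in standard software. No new data are needed, and the primary logistic regression and the 504 patients stay as planned.

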Confounding variables and effect modifiers*Pharmacological treatment.* The defined daily dose for each active ingredient is established during the follow-up period taking into account the number of days, the dosage, and the route of administration. The registered active ingredients belong to the following groups: antidepressants, anxiolytics, antidiabetics (oral, insulin), bronchodilators (selective agonists of Beta2 - adrenergic, anticholinergic), anti-inflammatories: corticosteroids, antihypertensives, and dyslipidemics.*Other associated comorbidities:* cardiac insufficiency, atrial fibrillation, cardiovascular disease, peripheral vascular disease, other chronic diseases.Participation in *other mental health therapies* given by psychologists and psychiatrists.*Anxiety* evaluated with the HARS-Hamilton Anxiety Rating Scale [42].*History of previous depressive episodes* (yes/no).

Cost variables

Expenses included in the cost-effectiveness analysis:*Use of primary care services*: consultation fees according to professional status and level of care.*Use of hospital services*: hospitalization and emergency room consultations.*Cost of psychotropic medication consumed during the study*: anxiolytics and antidepressants according to the current catalogue from the Pharmacist Association.*Derived costs*: training and supervision of the nurses responsible for leading the sessions, their working hours spent with the groups, and expenses related to material used in the sessions and given out to the participants. In order to calculate the cost of the resources 2016 Oblikue rates are employed [43].

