The economic analysis will be carried out with a cost-effectiveness analysis to compare the expenses incurred from the psychoeducation intervention with those from habitual clinical practice over 1 year. The QALYs (quality-adjusted life years) obtained from the EuroQol questionnaire will provide the variable of effectiveness. That of cost will be obtained by measuring all the direct expenses generated by the participants from both groups and including any other related information. For instance, primary care consultations, referrals to specialists, hospitalization, additional tests, analytical tests, and medication expenses. The ratios and incremental costs for the IG versus CG will be calculated. Prices will be based on those of 2016 as the Oblikue database is the most complete for that period. As the healthcare costs will be generated over various years a constant discount rate of 3% per year will be applied. Finally, for the items with the greatest presence in the overall cost, a deterministic sensitivity analysis will be carried out to ensure robustness and reliability of the results obtained [45].

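### The economic analysis contradicts itself on discounting and on which costs count, so the incremental cost and the ICER are not uniquely specified

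*Protocol article*

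**What the plan says.** All references are to the protocol article.

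**Horizon and discounting (Statistical analysis, economic paragraph).** The aim is to "compare the expenses incurred from the psychoeducation intervention with those from habitual clinical practice over 1 year". The same paragraph then states: "As the healthcare costs will be generated over various years a constant discount rate of 3% per year will be applied". It also fixes the price year: "Prices will be based on those of 2016 as the Oblikue database is the most complete for that period". QALYs from the EuroQol questionnaire are the effect measure. Discounting is stated for costs, and the text is silent on QALYs.

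**Cost scope, first version (Measures, cost variables).** This is an itemised list of what enters the cost-effectiveness analysis: primary care use, hospital and emergency use, intervention costs (training, supervision, nurse hours, materials), and one drug item, "Cost of psychotropic medication consumed during the study". That item is specified as anxiolytics and antidepressants, priced from the pharmacists' association's current catalogue. Tests and specialist referrals do not appear.

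**Cost scope, second version (Statistical analysis).** Cost is to cover every direct expense in both groups, with examples: "primary care consultations, referrals to specialists, hospitalization, additional tests, analytical tests, and medication expenses". The medication item has no psychotropic limit. Table 3 likewise lists pharmacological treatment under costs without a limit.

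**The concern.** The reason given for discounting does not fit the horizon. If each patient is costed over one year, no patient has costs in several years. Costs would span several years only because centres enter the trial at different dates, and that is no ground for valuing a later entrant's care at less, least of all at fixed prices.

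The two cost definitions cannot both be followed. The choice could matter here because every participant has type 2 diabetes, COPD, asthma or ischaemic heart disease, and the programme teaches adherence to treatment (Table 1, session 6). Use of antidiabetic, respiratory and cardiovascular drugs may therefore differ between arms. One definition counts that difference and the other leaves it out. If the scope stays open until the data are seen, it can also be chosen after the fact. Cost-effectiveness is a secondary objective, but a named one.

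**Working it through.** The article states no incremental cost or ICER, so there is no economic result to reproduce. The check sizes the discounting and sets the two cost definitions side by side.

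**1. Discounting**

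Inputs:
- rate r = 3% per year and a horizon of 1 year (Statistical analysis);
- last visit either 12 months after inclusion (Recruitment process, closing paragraph) or 12 months post-intervention (Study design). With 12 weekly sessions, about 3 months, the second is roughly 15 months from baseline.

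Formulas: a cost at time t is multiplied by (1.03)^−t. A cost spread evenly over T years is multiplied by [1 − (1.03)^−T] / [T × ln 1.03], with ln 1.03 = 0.02956.

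By patient time:
- T = 1, cost on the last day: 1/1.03 = 0.971, a reduction of 2.9%.
- T = 1, evenly spread: 0.02913 / 0.02956 = 0.985, a reduction of 1.5%.
- T = 1.25, last day: (1.03)^−1.25 = 0.964, a reduction of 3.6%.
- T = 1.25, evenly spread: 0.03627 / (1.25 × 0.02956) = 0.982, a reduction of 1.8%.

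By calendar time from trial start, the whole cost stream of a patient who enters k years late is scaled by (1.03)^−k:
- k = 1: 0.971 (2.9% lower);
- k = 2: 0.943 (5.7% lower);
- k = 3: 0.915 (8.5% lower).

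The delays k are assumptions. Recruitment began in September 2017 and no end date is given.

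These percentages apply to costs, not directly to the ICER. Over 12 months of patient time each arm's mean cost falls by between 0 and 2.9%, so the difference between arms moves by at most 2.9% of the larger arm's mean cost.

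**2. Cost scope**

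| Item | Measures, cost variables | Statistical analysis |
|---|---|---|
| Primary care use | yes | yes |
| Hospital use | yes | yes |
| Intervention costs | yes, itemised | yes, as the cost being compared |
| Anxiolytics, antidepressants | yes | yes |
| Other drugs | not listed | yes, as direct medication expense |
| Specialist referrals | not listed | yes |
| Additional and analytical tests | not listed | yes |
| Prices | current catalogue for drugs, 2016 rates for resources | 2016 |

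Write ΔC₁ and ΔC₂ for the incremental cost (intervention minus control) under the first and second definitions, at common prices. Then

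ΔC₂ = ΔC₁ + Δ(other drugs) + Δ(referrals) + Δ(tests),

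and the two ICERs differ by [Δ(other drugs) + Δ(referrals) + Δ(tests)] / ΔQALY. The documents give no unit costs or volumes, so none of these terms can be valued. Their signs are open too: drug use might rise with adherence, while referrals and tests might fall or rise.

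**The case against.** The strongest defence is that these are wording conflicts in a secondary objective. The second cost list consists of examples and speaks of medication expenses, not of all medication, so the itemised list under Measures could be taken as the definition. That reading is possible for the drug item, but the examples illustrate a rule that covers every direct expense, and they name referrals and tests that the itemised list lacks. The conflict remains.

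On discounting, the defence is that the effect is minor and neutral between arms. It is minor by patient time. By calendar time, patients are randomised within each centre, so both arms there share the same entry delay, and the rule rescales the cost difference without favouring an arm. This stands and limits the point. It does not remove the contradiction between several years and "with those from habitual clinical practice over 1 year".

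Some stronger readings may tempt a reader, but the documents do not support them:
- **That asthma admissions are left out of costs.** The phrase "due to complications arising from diabetes, COPD, and ischemic cardiopathy (yes/no" belongs to the healthcare-utilisation outcome. The hospital item in the cost list has no disease limit.
- **That the psychotropic-only list favours the intervention.** It also omits tests and referrals, which could move either way. The net direction is unknown.
- **That calendar-time discounting is planned, or that QALYs will go undiscounted.** The article gives no time base and is silent on QALYs.
- **That sampling uncertainty will be ignored.** The article says that "a deterministic sensitivity analysis will be carried out to ensure robustness and reliability of the results obtained", but not that this is the only expression of uncertainty. Bootstrap intervals, acceptability curves and baseline EQ-5D adjustment are commonly left to an analysis plan.

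**Conclusion.** The point holds as two internal contradictions: the reason for discounting conflicts with the one-year horizon, and cost scope and price year are each stated in two ways. The incremental cost and the ICER are therefore not uniquely specified. It would go too far to call them wrong or undefined, since each definition taken alone yields a usable result.

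The discounting part is small if time is counted per patient. The larger reductions, 5.7% or more, need calendar-time discounting with assumed entry delays of two years or more. The cost-scope part is the more important one: it can change the incremental cost, by an amount and in a direction that cannot be derived from the documents.

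**What to change.** 1. Delete discounting for the 12-month within-trial analysis and count time per patient. If follow-up is meant to run to 12 months post-intervention, state that horizon and apply one time base and one discounting rule to costs and QALYs alike.
2. Use one cost list in both sections: the scope in the Statistical analysis section, with all the drug groups registered under Measures, plus the intervention costs itemised there.
3. Use one price year for all items, drugs included.

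The cost is revised wording and a little more costing work. Defined daily doses for antidiabetics, bronchodilators, corticosteroids, antihypertensives and lipid drugs are already registered as confounders, so they need pricing rather than new collection. The change should be fixed before any cost data are analysed.

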### Sample size

A power analysis will be conducted to determine the appropriate sample size. A previous study of psychoeducation programs [18] reported a remission rate at 9 months follow-up of 40% in the IG and 26% in the CG. Assuming a 5 and 20% alpha and beta risk, respectively, 189 patients are required for each group. Due to a number of reasons, an approximately 25% dropout rate is expected, consequently, 252 participants per group need to be recruited (total *n* = 504). In addition, 25 PHC are required each with a mean of 20 patients (IG *n* = 10, CG *n* = 10).

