### Measures

The selected variables and instruments, as well as the evaluation program timeline, are detailed in Table 3. Data will be imported using an online survey tool and include:

**Table 3 Tab3:** Outcome measures

Outcome measures	Timeline		
	Pre-intervention	Post-intervention	
		3 mo	12 mo
1. Socio-demographic variables			
Sex, age, marital status, educational level, employment status, reference PHC	X		
2. Diagnostic variables			
Diagnosis depression: MINI	X		
Diagnosis chronic physical illness: ICD-10	X		
Suicide risk: MINI	X		
Cognitive impairment: Pfeiffer questionnaire	X		
3. Clinical variables			
Depressive symptoms: BDI- II questionnaire	X	X	X
Anxiety symptoms: HARS questionnaire	X	X	X
Quality of life: EQ-5D-5 L questionnaire	X	X	X
Pharmacotherapy	X	X	X
Therapeutic compliance: Morinsky-Green test	X	X	X
Feasibility of the intervention	X	X	
4. Blood test and Physical parameters			
Type 2 diabetes mellitus: Analytical HBA1C	X		X
COPD: FEV1 and Medical Research Coincil (mMRC)	X		X
Asthma: Spirometry and Peak flow	X		X
Ischemic heart disease: Analytical cholesterol LDL and Blood pressure	X		X
5. Costs variables			
Pharmacological Treatment	X	X	X
Utilization of services: PHC and hospital	X	X	X
Other comorbidities	X		X
Costs derived from the intervention	X	X	X

*Abbreviations*: *mo* months, *BDI-II* Beck Depression Inventory secondary edition, *COPD* Chronic obstructive pulmonary disease, *EQ* EuroQuol, *FEV1* Forced expiratory volume, *HARS* Hamilton Anxiety Rating Scale, *HBA1C* Hemoglobin A1C test, *ICS-10* International classification of diseases-10th revision, *MINI* Mini international neuropsychiatric interview, *PHC* Primary Healthcare Centers

Diagnostic variables*Diagnosis of depression* according to the MINI interview [27, 28].*Physical diseases* (code CIE-10). Diagnosis of diabetes mellitus (E11-E14 and sub-groups), COPD (J43-J44 and sub-groups), asthma (J45), and/or ischemic cardiopathy (I20-I25 and sub-groups) as registered in the patients’ medical records and confirmed by their family doctor [29].*Risk of suicide* evaluated by the MINI interview [27, 28].*Pfeiffer Scale* to detect cognitive impairment [30, 31]. This is a hetero-administered questionnaire made up of 10 items and scored from 0 to 10 (errors). From 5 onwards an individual is considered to present moderate/severe cognitive decline.

Socio-demographic variables:

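### The robustness check stated for the economic result varies cost items only, so it cannot show whether the QALY difference or the ratio is distinguishable from chance

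*Protocol article*

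**What the plan says.** All references are to the protocol article.

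- **Effect measure** (Statistical analysis, economic paragraph): "The QALYs (quality-adjusted life years) obtained from the EuroQol questionnaire will provide the variable of effectiveness". The intervention's expenses are compared "with those from habitual clinical practice over 1 year".
- **Result reported** (same paragraph): "The ratios and incremental costs for the IG versus CG will be calculated".
- **Robustness** (same paragraph, last sentence): "for the items with the greatest presence in the overall cost, a deterministic sensitivity analysis will be carried out to ensure robustness and reliability". No other robustness or uncertainty step is given for the economic analysis.
- **Neighbouring clinical analysis** (Statistical analysis, first paragraph): "Variable differences in the BDI-II rating and other scores with respect to baseline will be calculated", after which Student's "t test will be employed for the comparison between the groups" on these variables.
- **Data** (Measures, Table 3): the row "Quality of life: EQ-5D-5 L questionnaire" and the row for use of primary care and hospital services are both marked at baseline, 3 months and 12 months.

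**The concern.** A deterministic sensitivity analysis changes an input by a chosen amount and recalculates the result. Applied to the largest cost items, it answers one question: would the result change if those prices or quantities were different? It does not ask whether another sample of patients would have given a different QALY difference or a different cost difference. The article nevertheless presents it as the step that secures the robustness and reliability of the results as a whole.

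The QALY difference is the denominator of the ratio, and in a trial of this size it may be small relative to its standard error. If so, the ratio can look stable across every cost scenario and still be compatible with no QALY gain. Cost-effectiveness is a named secondary objective (Abstract; Background), so its result should carry a measure of uncertainty that fits the claim made for it.

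**Working it through.** **1. Number of patients, from the plan's own figure.** The Sample size section states: "Assuming a 5 and 20% alpha and beta risk, respectively, 189 patients are required for each group". Inputs there: 40% versus 26% remission and 25% dropout.

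- Two-sided 5%, 80% power, pooled variance: n = [1.960·√(2·0.33·0.67) + 0.842·√(0.40·0.60 + 0.26·0.74)]² / 0.14² = 176 per group.
- With continuity correction: 190 per group, against 189 stated. The figure is reproduced to within one patient.
- Dropout: 189 / 0.75 = 252 per group, exactly as stated.

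So 189 evaluable and 252 recruited per group can be used below. The economic section gives no figure of its own.

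**2. What the stated check can move.** Write the ratio as ΔC/ΔQ. Varying cost items changes ΔC. ΔQ is calculated from EuroQol data and contains no cost item, so its value and sign stay the same in every cost scenario. The standard errors of ΔC and ΔQ do not enter a deterministic analysis at all.

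**3. Size of the uncertainty left out.** The documents give no standard deviation for the one-year QALY. Assumed range: 0.15 to 0.25. With independent patients, SE = SD·√(2/n) and the 95% half-width is 1.96·SE.

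| Assumed SD | SE, n = 189 | Half-width, n = 189 | Half-width, n = 252 |
|---|---|---|---|
| 0.15 | 0.0154 | 0.030 | 0.026 |
| 0.20 | 0.0206 | 0.040 | 0.035 |
| 0.25 | 0.0257 | 0.050 | 0.044 |

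Widening the assumption to 0.10–0.30 gives 0.020 to 0.060 with 189 per group. Clustering by centre or therapy group would widen these figures, and adjustment for baseline EQ-5D would narrow them.

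**4. The two uncertainties on one scale (illustration, all money figures assumed).** At 25,000 euros per QALY, half-widths of 0.0302 and 0.0504 are worth 0.0302 × 25,000 = 755 euros and 0.0504 × 25,000 = 1,260 euros per patient. If the incremental cost were 200 to 400 euros, a 30% change in it would move net benefit by 60 to 120 euros. On these figures the stated check explores a range several times smaller than the sampling uncertainty in the QALY term alone.

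**The case against.** **A condensed article may leave intervals to a fuller plan.** The article does not say that the ratios come without intervals, and bootstrap methods or acceptability curves are details that a full analysis plan could hold. This stands as far as it goes: the absence of those details is not the point. The article does, however, name a method and state its purpose, and that method cannot serve that purpose. The sentence needs correcting whatever the fuller plan contains.

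**The QALY difference is tested elsewhere.** A reader might infer that the effect is never tested. The documents do not support that. EQ-5D-5L is a scored secondary outcome, and the planned t tests on changes in other scores can be read to include it. But a change score at one visit is not the one-year QALY, and a t test on it says nothing about the cost difference or the ratio.

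**A chance gain would be declared robust half the time.** A reader might infer this, because with no true effect the observed QALY difference is positive in 50% of trials. That 50% holds for any symmetric, unbiased difference and says nothing special about this plan. The article sets no threshold and no rule for calling the programme cost-effective or a result robust, so no false-claim rate can be derived from it. Nor can one assume a programme with no net cost: if it has no effect there are no savings to offset the nurse time, and 12 sessions × 1.5 h × 2 nurses already come to 36 nurse-hours per group.

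**Two further inferences fail.** A negative ratio is not ambiguous here, since incremental costs are reported beside it. The Discussion's remarks on wider use are tied to effectiveness being shown, not to the cost ratio.

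**Conclusion.** The point holds in a limited form. The one robustness step stated for the economic analysis is deterministic and confined to costs. It cannot show whether the incremental QALY, or the ratio built on it, is distinguishable from chance, and no test or interval is stated for the incremental QALY, the incremental cost or the ratio.

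The uncertainty left out is a 95% half-width of about 0.03 to 0.05 QALY. This rests on an assumed standard deviation of 0.15 to 0.25, 189 evaluable patients per group and independence between patients. That the check cannot move the QALY difference needs no assumption. The documents do not support any stated probability of a wrong cost-effectiveness claim. Only a secondary objective is affected. This is a cheap improvement.

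**What to change.** Replace the last sentence of the economic paragraph so that it says the following:

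1. The main uncertainty analysis is a non-parametric bootstrap of patient-level cost and QALY pairs that respects clustering by centre, for example by resampling whole primary healthcare centres. Resampling within each arm of each centre is less suitable. A cell of 10 patients falls to about 7.5 after 25% loss, and resampling such cells understates the standard error by about 7% (√(1 − 1/7.5) = 0.93) and holds the therapy groups fixed.
2. Incremental cost, incremental QALY and incremental net benefit over a stated range of thresholds are reported with 95% intervals, together with an acceptability curve.
3. The deterministic analysis is a secondary check of cost assumptions only.

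No new data are needed, since EQ-5D-5L and service use are already collected at baseline, 3 and 12 months. The cost is a change of wording and a few hours of programming. The downside is that the cost-effectiveness statement may turn out less definite.
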